## Abstract

**Background:**

Isolated systolic hypertension is a highly prevalent disease among the elderly. The little available evidence on the efficacy of nitrates for treating the disease is based on small experimental studies.

**Methods/design:**

We performed a multicenter, randomized, double-blind, phase III, placebo-controlled trial in 154 patients aged over 65 years with refractory isolated systolic hypertension. Patients were randomized to placebo or 40 mg/day of extended-release isosorbide mononitrate added to standard therapy and titrated to 60 mg/day at week 6 if blood pressure exceeded 140/90 mmHg.

The primary objective was to assess the effect on clinical pulse pressure of extended-release isosorbide mononitrate added to standard therapy in patients aged over 65 years with refractory isolated systolic hypertension after 3 months of treatment.

The secondary objectives were as follows: to quantify the effect of adding the study drug on central blood pressure and vascular compliance using the augmentation index and pulse wave velocity; to evaluate the safety profile by recording adverse effects (frequency, type, severity) and the percentage of patients who had to withdraw from the trial because of adverse events; to quantify the percentage of patients who reach a clinical systolic blood pressure <140 mmHg or <130 mmHg measured by ambulatory blood pressure monitoring; and to quantify the change in pulse pressure measured by ambulatory blood pressure monitoring.

**Discussion:**

Few clinical trials have been carried out to test the effect of oral nitrates on isolated systolic hypertension, even though these agents seem to be effective. Treatment with extended-release isosorbide mononitrate could improve control of systolic blood pressure without severe side effects, thus helping to reduce the morbidity and mortality of the disease.

**Trial registration:**

EUDRACT Number: 2012-002988-10

## Background

Hypertension is responsible for many deaths worldwide [1,2]. It is very prevalent in Spain and is estimated to affect more than 25% of adults [3,4]. In the United States, more than 60% of people aged over 65 years are hypertensive. The most prevalent type of hypertension is isolated systolic hypertension (ISH), which has a frequency that increases with age and can reach over 80% in octogenarian patients [5]. Loss of arterial elasticity accompanied by increased arterial stiffness is the main pathogenic mechanism in ISH, which is characterized by high systolic blood pressure (SBP) (≥140 mmHg) and normal diastolic blood pressure (DBP) (<90 mmHg), with a consequent increase in differential pressure, or pulse pressure (PP), the main predictor of cardiovascular complications in older people [6]. The mechanism responsible for the decrease in arterial compliance is the subject of debate and has been considered to be purely structural (that is, secondary to the calcification produced by age in the walls of large arteries) or partly functional (that is, due to endothelial dysfunction and increased smooth muscle tone).

Treating ISH is beneficial, as it can reduce both cardiovascular morbidity and total mortality [7], even in much older people [8]. Besides the widespread recommendation to reduce SBP to less than 140 mmHg, there is no evidence from clinical trials to support this recommendation in older people, since none of the studies demonstrating a benefit included patients with an SBP between 140 and 160 mmHg [9]. No first-line antihypertensive treatments can produce a clinically relevant reduction in arterial compliance and, therefore, PP, [10,11], with the result that treatment options are limited. The decrease in SBP is accompanied by declines in DBP that can compromise coronary perfusion and increase the risk of coronary complications, which is again a limiting factor for current treatments. It seems reasonable to assume that a drug that decreases both SBP and PP could have additional benefits in the treatment of ISH. The value of such an approach could be proven in the short term by demonstration of changes in vascular function parameters (augmentation index (AI) and pulse wave velocity (PWV)) and in the long term by documenting a reduction in cardiovascular morbidity and mortality.

Nitrates have been used for many years to treat patients with angina pectoris, acute coronary syndrome, and acute lung edema. These agents are not generally used to treat hypertension, except in emergency cases, in which case they are used intravenously to produce a rapid decrease in blood pressure, although tachyphylaxis occurs within a few days of treatment. All nitrates, as donors of nitric oxide (NO), produce intense arterial vasodilation associated with direct effects on smooth muscle cells, by activating guanylyl cyclase to form cGMP, which inhibits calcium entry into the cell. The most common adverse events are headache and hypotension, although dizziness, nausea, fatigue, weakness, and tachycardia can also be observed.

Currently available tools enable us to evaluate vascular function and central hemodynamics non-invasively. Central blood pressure (CBP) can be measured in larger arteries using pulse wave analysis, and available data suggest a closer relationship between CBP and cardiovascular morbidity and mortality [12]. Additionally, PWV, which is the best parameter for measuring arterial elasticity [13,14], can be measured non-invasively and provides an accessible and exhaustive evaluation of arterial stiffness, which is the underlying pathogenic mechanism of ISH [15].

Our literature review revealed only five mini-trials assessing the effect of nitrates on blood pressure (BP) and control of ISH. Sample sizes were small and the studies were not performed in the context of refractory ISH [16-20]. The results provide some evidence of the possible use of exogenous NO donors to decrease the reflected wave amplitude and PP [16-22]. Use of nitrates could have a beneficial effect on the control of ISH (as SBP falls with almost no change in DBP), with a possible reduction in cardiovascular morbidity and mortality.

Therefore, we designed a study to evaluate the effect on PP and vascular function (CBP, AI, and PWV) of the addition of extended-release isosorbide mononitrate to standard treatment in older patients with refractory ISH. Refractory hypertension is defined as uncontrolled hypertension in patients using three or more antihypertensive drugs (one of which is a diuretic) at the maximum dosage; we changed our protocol to include patients receiving low doses of diuretic and maintaining at least two more drugs, since most patients never use diuretics at the maximum dosage (for example, hydrochlorothiazide at 50 mg/day).

If a beneficial effect is demonstrated, a study of morbidity and mortality would be justified.

### Hypothesis

The addition of extended-release isosorbide mononitrate to standard antihypertensive treatment in patients with refractory ISH produces a positive effect on vascular function, resulting in reduced PP and improved CBP, AI, and PWV.

### Aims

The primary objective of our study was to compare the effect of extended-release isosorbide mononitrate on clinical PP with that of a placebo, in addition to the standard treatment, in patients over 65 with refractory ISH after 3 months of treatment.

The secondary goals were as follows:

1. To quantify the effect of extended-release isosorbide mononitrate on vascular function (estimated using CBP, AI, and PWV).

2. To evaluate the safety profile by estimating the frequency, type, and severity of adverse events and the percentage of patients who had to withdraw from the study because of adverse events, in particular headache and orthostatic hypotension.

3. To determine the percentage of patients who reach clinical SBP <140 mmHg in both treatments groups.

4. To determine the percentage of patients who reach a 24-hour mean SBP <130 mmHg (measured using ambulatory blood pressure monitoring (ABPM)) in both treatment groups.

5. To measure the change in PP using ABPM.

## Methods/design

Ours is a phase III, multicenter, randomized, double-blind, placebo-controlled trial performed in several primary care centers in the Regional Community of Madrid and in Hospital La Princesa, Madrid. The trial is registered in the EU Clinical Trials Register (EUDRACT Number: 2012-002988-10), and the protocol was approved by the Clinical Research Ethics Committee of the Regional Community of Madrid.

The study was designed to evaluate the efficacy and safety of a marketed drug in a therapeutic indication different from that for which it is approved. The objective of the study was to evaluate, after 3 months of appropriate treatment, the effect of adding extended-release isosorbide mononitrate to standard treatment in patients with resistant ISH. No recommendations have been made on the treatment of these patients; therefore, we designed a study to compare the net effect of the study drug with that of placebo.

### The study began in January 2013 and is ongoing

#### Participants

The study population comprises patients aged ≥65 years of both genders attended at primary care centers or at the Hypertension Unit of Hospital La Princesa. All patients give their written informed consent to participate in the study. Patients are included if they meet all the inclusion criteria and none of the exclusion criteria. Table 1 shows the inclusion and exclusion criteria .

**Table 1 T1:** Inclusion and exclusion criteria

**Inclusion criteria**	**Exclusion criteria**
Aged 65 or over	Current treatment with nitrates, intolerance to them or contraindication to their use
Refractory ISH: SBP ≥140 mmHg and DBP <90 mmHg and SBP in ABPM ≥130 mmHg, despite treatment with three drugs at maximum dosage, one of them diuretic, during at least one month before the start	Concomitant treatment with phosphodiesterase 5 inhibitors
	SBP ≥180 mmHg
Good adherence to treatment, defined as a good response to all questions of Morisky-Green’s test	Permanent atrial fibrillation
	Secondary hypertension
Life expectancy greater than 1 year	Congestive heart failure, grade III-IV NYHA
Signing the informed consent	Chronic kidney disease with glomerular filtration rate ≤30 ml/min, estimated by MDRD
Ability to understand study procedures and to comply with them for the entire length of the study	
	Liver insufficiency
	Active cancer
	Anemia ≤8 g/dl
	Simultaneous participation in another clinical trial
	Not signing the informed consent
	Any other circumstance that, according to the research criteria, advises against the inclusion to the study

Patients are included if they meet all the inclusion criteria and none of the exclusion criteria.

ABPM: ambulatory blood pressure monitoring, DBP: diastolic blood pressure, ISH: isolated systolic hypertension, NYHA: New York heart association, MDRD: modification of diet in renal disease, SBP: systolic blood pressure.

#### Variables

Variables reported for trial participants include the following:

1. Demographic characteristics: sex, age, height, weight, body mass index, waist circumference, and smoking and drinking habits, at screening.

2. Antihypertensive treatment and concomitant treatments, at screening.

3. Medical history: presence of macrovascular or microvascular disease and diabetes mellitus or dyslipidemia.

4. Laboratory tests: hematology and biochemistry with kidney and liver function markers to assess that the patient meets all the inclusion criteria (screening visit).

5. BP measurement at baseline, 6 weeks, and completion (SBP, DBP, PP, and heart rate (mean of 3) while seated and 1 minute after standing). Monitoring is performed between 8 am and 10 am, before patients take their medication.

6. 24-hour ABPM (Spacelabs device, OSI systems company, US; http://www.spacelabshealthcare.com/): mean of SBP, DBP, heart rate, and PP during activity and at rest (baseline and completion). Patients take their antihypertensive medication as usual.

7. CBP, PWV, and AI at visits 1 and 3 (measured with the patient lying supine using a Sphygmocor device, AtCor Medical, Australia; http://www.atcormedical.com/).

8. Adherence to treatment (Morisky-Green test) at screening and at visits two and four.

9. Side effects: any adverse event during administration of the study drug, in particular headache and orthostatic hypotension.

#### Randomization, blinding, and assignment to treatment groups

Subject numbers are assigned sequentially as each patient enters the study. Subjects are assigned to the study drug through a randomization schedule based on the randomization plan. The study drug is stored under the conditions specified on the label in a locked, safe area of the pharmacy department to prevent unauthorized access.

Both the study drug and the placebo are indistinguishable; they are manufactured by the same company and are similar in appearance, organoleptic characteristics, and presentation.

In the event of an emergency, the investigator decides whether it is necessary to unblind the subject’s treatment assignment using the unblinding envelopes provided to the hospital and/or pharmacy. If unblinding is necessary, the investigator or study pharmacist must record the reason for unblinding, as well as the date and time of the event.

During the study, the events considered sufficient reason for unblinding are as follows: admission to hospital or visit to the emergency department related to the study drug. The patients can be removed from the study without unblinding in the following circumstances: withdrawal of consent, major adverse event(s), ineligibility (arising either during the study or retrospectively after having been overlooked at screening), significant protocol deviation, disease progression requiring discontinuation of the study medication or inability to continue to comply with study procedures, loss to follow-up, or death. Each participant has the right to withdraw from the study at any time, for any reason, and with no repercussions for his/her medical care.

In the case of unblinding, the analyses are based on an intent-to-treat population, which includes all randomized subjects. Because the percentage of lost participants was predicted in the calculation of sample size, lost patients need not be replaced during follow-up. The person analyzing the results remains blind to the patient’s group.

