#### Trial intervention

When all of the procedures at the inclusion visit are performed, the patients are sent to the investigator responsible for assessing vascular function (PWV, AI, and CBP), randomization, and delivery of the study medication (12-week supply). Vascular function parameters are measured by the same trained investigator to ensure consistency and homogeneity.

Before administration of the drug, the investigator explains the most common adverse events (headache and orthostatic hypotension) to the patient.

After randomization, a single 40-mg dose of extended-release isosorbide mononitrate is administered between 9:30 and 10:30 am during the first 6 weeks. Study patients attend three visits after randomization. The first is at 6 weeks from baseline, when clinical parameters are assessed. These include BP (seated and standing), resting pulse, and the Morisky-Green test. All adverse events are recorded, regardless of their relationship to the study medication. If the objective (SBP <140 mmHg) is not reached, the dose is titrated to 60 mg/d (single dose); otherwise, the 40-mg dose is maintained.

After 12 weeks of treatment, the study is considered to have finished, except in the case of patients who withdraw prematurely. At the final visit, the parameters recorded are PP, SBP, DBP, heart rate and ambulatory BP. Compliance is also evaluated using the Morisky-Green test, and the investigator questions the patient about adverse events, orthostatic hypotension, and other treatments taken during the study. Vascular function parameters (CBP, AI, and PWV) are measured between 2 and 5 days before the final visit while the patient is still taking the medication.

Figure 1 shows the study flow-chart.

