#### Sample size calculation

Sample size is predetermined based on the effect the variable PP, which is the primary objective. According to the results of the Starmans-Kool trial [17], the PP after treatment could be 87 mmHg in the placebo group and 79 mmHg in the experimental group, both with a standard deviation of 16 mmHg. In order to obtain a power of 80% to detect differences using a *t* test for independent samples, with an α risk of 5%, the sample size for each group must be 64 patients. Considering losses of 20% of recruited individuals, which could weaken the sample for some secondary objectives, we decided to increase the sample size by this percentage, although all the tests are performed by intent to treat. For this reason, the final sample size for each group is 77 patients.

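### Removal from the study, not only from study drug, leaves no stated week-12 clinic pulse pressure for patients whom the intent-to-treat analysis is meant to include

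*Protocol article*

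**What the plan says.** All references are to the protocol article.

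- **Removal.** The section on randomization, blinding and assignment says "The patients can be removed from the study without unblinding in the following circumstances: withdrawal of consent, major adverse event(s". The list continues with "ineligibility (arising either during the study or retrospectively after having been overlooked at screening), significant protocol deviation", disease progression that makes study medication stop, inability to keep up with procedures, loss to follow-up and death.
- **Analysis population.** The same section states that "the analyses are based on an intent-to-treat population, which includes all randomized subjects". That sentence opens with a condition about unblinding, but the sample size section makes the commitment general: "although all the tests are performed by intent to treat".
- **Measurement times.** The Variables section lists "BP measurement at baseline, 6 weeks, and completion". The section on evaluation of effectiveness compares baseline with final-visit values for every objective.
- **Premature withdrawal.** Under Trial intervention: "After 12 weeks of treatment, the study is considered to have finished, except in the case of patients who withdraw prematurely". No later blood pressure visit is given for these patients. The only follow-up described after withdrawal, in the safety section, is of related adverse events.
- **Expected losses.** The Discussion names possibly high loss from non-fatal side effects as a limitation and says the sample size calculation compensates for it. The sample size section allows for 20% loss and mentions its effect only on some secondary objectives.
- **Missing data.** Item 5 of the statistical analysis section provides a sensitivity analysis, without detail.

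**The concern.** An intent-to-treat analysis needs the outcome of patients who stopped treatment. Several of the removal grounds do not prevent a clinic PP reading at week 12: a patient with a major adverse event, a late-found eligibility failure or a protocol deviation can often still attend. If such a patient leaves the study altogether, the value is lost by rule.

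The loss is unlikely to be random. The article itself singles out headache and orthostatic hypotension as the adverse events to watch, and it expects side effects to cause loss. More active than placebo patients may therefore go missing, and they may differ in PP from those who stay. The link to treatment is less clear for ineligibility and deviations, but removing those patients also departs from analysing everyone as randomised.

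At stake is the primary comparison of week-12 clinic PP. A visit that was never held cannot be recovered by a later analysis plan.

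**Working it through.** **Inputs** (sample size section): PP 87 mmHg on placebo and 79 mmHg on active drug, so a difference of 8; SD 16; α 5%; power 80%; 64 per group, raised to 77 for 20% loss.

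**Step 1. The plan's own figure.** The normal approximation, n = 2(1.96 + 0.8416)² × 16²/8² = 62.8, gives 63. The exact two-sided t test has power 79.5% at 63 and 80.1% at 64 per group, so 64 is reproduced. The 77 is 64 × 1.2 = 76.8, rounded up. (Dividing by the retained fraction would give 64/0.8 = 80; that is a separate matter.)

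**Step 2. What the allowance covers.** At 20% loss, 77 × 0.8 = 61.6 per arm have a week-12 PP, and 154 × 0.2 = 30.8, about 31 patients, do not. Exact power is 78.2% at 61 and 78.9% at 62 per arm. With an assumed 30% active and 10% placebo loss (54 versus 69 patients) it is 77.9%. Precision is therefore nearly preserved, and precision is all that the allowance addresses.

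**Step 3. Bias from selective loss.** Let a fraction d of an arm be removed, and let their week-12 PP be k mmHg higher than that of patients who stay. The full-arm mean is then the stayers' mean plus d × k. A comparison of observed values only is shifted, in favour of active drug, by

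shift = d(active) × k(active) − d(placebo) × k(placebo).

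The documents give neither the loss in each arm nor k, so these are assumptions:

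| Assumption | k = 4 | k = 8 | k = 16 |
|---|---|---|---|
| 20% loss in both arms, same k | 0 | 0 | 0 |
| 25% active, 15% placebo, same k | 0.4 | 0.8 | 1.6 |
| 30% active, 10% placebo, same k | 0.8 | 1.6 | 3.2 |
| 20% active loss, selective in the active arm only | 0.8 | 1.6 | 3.2 |

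The sign can reverse. If disease progression removed 30% of placebo and 10% of active patients, with k = 8 in both arms, the shift would be 1.6 mmHg against the drug.

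**Step 4. What keeping the visits does to the estimate.** If all 77 per arm have a week-12 PP and the full 8 mmHg holds, exact power is 86.9%. If active patients who stop drug lose the whole effect (assumption; SD still 16), the all-randomised difference is 8 × (1 − fraction stopping):

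| Active patients who stop | Difference | Power at 77 per arm |
|---|---|---|
| 10% | 7.2 mmHg | 79% |
| 20% | 6.4 mmHg | 69% |
| 30% | 5.6 mmHg | 58% |

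**The case against.** A reader might infer that the removal rule and the intent-to-treat promise are incompatible, or that the primary analysis becomes a comparison of completers. The text supports neither. An analysis of all randomised patients can coexist with missing values if these are handled analytically. The article mentions a sensitivity analysis, some removed patients will have a week-6 PP, and no section plans a completers' analysis. The detail of missing-data handling properly belongs in the full protocol or analysis plan, which are not shown.

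The absence of a week-12 PP is also inferred. The removal wording is permissive, the safety section speaks both of withdrawal from the study and of withdrawal from treatment, and the flow-chart is not visible. This stands as a reason for moderate wording. Nothing shown provides a later reading, however, and the Discussion treats side effects as a cause of loss to follow-up.

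Finally, the removal list is, apart from the investigator's judgement on adverse events, the only stopping list shown. Deleting items from it could remove the stated basis for stopping a patient's drug. That objection holds, so the change should concern data collection only.

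**Conclusion.** The point holds as a weakness in data collection that undermines the promised analysis. Patients may be removed from the study for reasons that need not end follow-up, no clinic PP is described after removal, and a larger sample does not correct selective loss. The article is also wrong to treat losses as compensated for, and to mention them only for secondary objectives: the primary outcome is lost as well.

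About 31 of 154 patients are affected if the planned 20% loss occurs and none of the lost patients is measured at week 12. The bias figures of 0.8 to 3.2 mmHg are illustrations. A reader might infer from Step 4 that the plan will overstate the effect by 20 to 30%, since observed values would show 8 mmHg where the all-randomised difference is 6.4 or 5.6. The documents do not support that as a prediction: it rests on patients who stop losing the whole effect while those who stay gain the full 8 mmHg, it ignores placebo losses, and the true direction is open.

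**What to change.** Reconcile the sections on randomization and blinding, trial intervention, safety, sample size and the Discussion so that stopping study drug and ending data collection are two separate events. Then state:

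- Every randomised patient who stops study drug, has not withdrawn consent to follow-up and is able to attend keeps the scheduled week-6 and week-12 clinic PP measurements.
- These values are analysed in the randomised arm, including those of patients found ineligible or with protocol deviations, which are recorded as such.
- The 20% allowance is described as protecting precision, for the primary outcome too, and not as compensating for selective loss.

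Leave the grounds for stopping study drug unchanged.

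**Cost.** A short amendment and a few more attended visits, all of which already exist in the schedule. Recruitment is still open, so it can take effect. The estimate may be smaller than 8 mmHg, with power below 80% in the scenarios of Step 4, and the team should accept this openly or revisit the sample size. Some bias can remain, because withdrawn consent, true loss and inability to attend will still leave gaps.
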